## 6 CONDUCT OF THE RESEARCH

| Persons whose consent is sought              | Who informs and collects the consent of the person                                                                                                                                        | When the person is informed                                   | When the consent of the person is obtained                                                                                                                                                                     |
|----------------------------------------------|-------------------------------------------------------------------------------------------------------------------------------------------------------------------------------------------|---------------------------------------------------------------|----------------------------------------------------------------------------------------------------------------------------------------------------------------------------------------------------------------|
| The person who lends himself to the research | The principal investigator or collaborator who is a registered and research-trained physician (pulmonologists, internists, infectious disease specialists and intensive care specialists) | Selection visit as part of the treatment at the time of care. | After a reasonable period of reflection with the patient, knowing that the care of these patients will have to be rapid and the sooner the procedure is put in place, the more convincing the results will be. |

## 6.1 Research Timeline

### 6.1.1 Inclusion visit.

For 18 months following the validation of the ethics committee, patients meeting the criteria and admitted to the COVID ward or intensive care in the 21 centers within the 11 hospitals in France and Mexico referenced for this study will be offered to participate in the study orally after verification of the inclusion and non-inclusion criteria and then a written consent will be collected. Notification of the patient's participation in this study will be listed in the patient's medical record.

We will collect:

**Socio-demographic data:** age, sex, weight, height, date of onset of symptoms, date of hospital admission

**Constants:** systolic blood pressure (SBP), diastolic blood pressure (DBP), heart rate (HR), body temperature, respiratory rate (RH), oxygen saturation, oxygen therapy flow.

Collection of the date of the last chest CT scan before inclusion with percentage of lung parenchyma involvement on CT images. Chest CT scan is not required for the study if the patient has not had one.

**Biology:** white blood cell counts, serum creatinine, D-Dimer, AST, and ALT (liver enzymes). This assessment will be collected, if it exists, made within the usual framework.

**Medical history:** chronic respiratory disease, cardiovascular disease, liver disease, diabetes and cancer or hematopathy under treatment.

Randomization will be done following the collection of written consent, via Cleanweb software.

### 6.1.2 Follow-up visits

From this point on, patients in the interventional group (Group A) will be instructed to spend at least 6 hours on their stomach (PP). They will put themselves in the position. They will stand on their stomach with their head turned to the side and a cushion placed under the chest at their convenience and will regularly note the time spent in PP. They (or the nurse in charge) will have at their disposal a collection sheet and a pen.

Patients in the control group (Group B) will do as usual without external intervention on the positioning to be adopted.

For a maximum of 28 days, a daily reading of the

- Vital status
- Transfer to intensive care for patients included in a ward unit

- Use of intubation
- Use of an alternative ventilation technique (NIV, high-flow nasal oxygen therapy)
- Maximum Oxygen Therapy Flow Rate (Nasal or Mask)

At the end of the stay (maximum on the 28th day): we will collect

- Length of ICU stay
- Length of hospital stay

If the patient is discharged before day 28 (maximum duration of study participation)

- Your vital status will be searched for up to 2 months after discharge by phone call

The total duration of the study will be 19 months.

|                                       |                                                              |
|---------------------------------------|--------------------------------------------------------------|
| Length of Inclusion Period            | 18 months                                                    |
| Duration of participation of subjects | 28 days                                                      |
| Search for vital status               | Up to two months after discharge from hospital by phone call |

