## 4 RESEARCH DESIGN

### 4.1 Primary endpoint

**Composite Outcome** : Achievement of one of the following criteria (if absent at the time of randomization):

- Use of intubation
- Death

Criteria assessed up to 28 days after inclusion

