| Telephone call for vital status if patient discharged from hospital before 28 days                   |                    |                                |                                | ✓                                   |

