## **9 EVALUATION OF EFFECTIVENESS**

### **9.1 Description of efficacy endpoints**

**Composite Outcome** : Achievement of one of the following criteria (if absent at the time of randomization):

- Use of intubation
- Death

Criteria assessed up to 28 days after inclusion

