## 9.2 Methods and planned timelines for measuring, collecting, and analyzing efficacy endpoints

The evaluation parameters are provided for in the case report form and will be collected by the designated investigators from the time of inclusion until the 28th day of participation. A telephone call may be made to the patient if he or she has been discharged from hospital before the 28th day in order to collect his or her vital status.

The data noted by the patient on the "time spent in PP" data collection sheet will be collected regularly in the paper CRF by the investigators.

The data collection in the e-CRF will be done by a TEC of the F-Widal-Lariboisière CRU, following the sending of the CRF pages by the centres by photos or scans with anonymised data.

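### After a discharge before day 28 the protocol specifies collection of vital status only, so a non-fatal intubation or readmission inside the 28-day endpoint window can be missed

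*Protocol*

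**What the plan says.** **Endpoints.** Section 4.1 makes the primary outcome a composite of death and "Use of intubation". Sections 4.1 and 9.1 both set the window: "Criteria assessed up to 28 days after inclusion". Nothing limits it to the index stay. Section 4.2 adds four counts of days alive over the same 28 days: without invasive ventilation, out of intensive care, out of hospital, and without NIV or high-flow oxygen.

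**Collection in hospital.** Section 6.1.2 provides "For a maximum of 28 days, a daily reading of the" vital status, ICU transfer, intubation, NIV or high-flow use and maximum oxygen flow. ICU and hospital stay are recorded once: "At the end of the stay (maximum on the 28th day): we will collect" them.

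**Collection after discharge.** Three places describe it, and all three name vital status only:
- Section 6.1.2: "Your vital status will be searched for up to 2 months after discharge by phone call".
- Schedule table (the second Section 6.1): "Telephone call for vital status if patient discharged from hospital before 28 days", ticked only in the last column, which runs to two months after inclusion.
- Section 9.2: "A telephone call may be made to the patient if he or she has been discharged from hospital before the 28th day", for the purpose of learning vital status.

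Section 8.2, under its paragraph on monitoring methods, again counts the two months from discharge.

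**The concern.** The endpoint window and the stated data collection do not match. A patient leaves hospital on day 8, is readmitted elsewhere, is intubated on day 12 and is alive at day 28. This patient has had a primary event, but the vital-status call returns only that the patient is alive. The record then shows no event, and the days from day 8 onward count as out of hospital, out of ICU and free of ventilation.

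The intubation component of the primary endpoint and the four day counts are exposed. The trial is open-label, so staff who know the allocation decide discharge, and loss need not be equal between arms. The interim analyses every 50 patients use patients followed to the primary endpoint. No contact is fixed at day 28, so the point at which a discharged patient's endpoint is complete is not defined. A statistical analysis plan cannot repair this, because it cannot recover data that were never requested.

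**Working it through.** **1. What each item would capture for a patient discharged alive before day 28**

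| Event between discharge and day 28 | Route named in the protocol |
|---|---|
| Death | Vital-status call, if made and if the death is dated |
| Intubation, patient then dies by day 28 | Counted through death, on the same conditions |
| Intubation, patient alive at day 28 | None |
| Readmission, ICU return, NIV or high-flow use | None |
| No readmission | Hospital, ICU and invasive-ventilation day counts follow from discharge date plus vital status; the NIV/high-flow count does too, assuming none is used at home |

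The exposed group is patients readmitted before day 28 and still alive at day 28 (or, for the day counts, readmitted for any time before death).

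**2. The plan's own sample size**

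Inputs from Section 13.1: 25% against 15%, power 80%, maximum N = 500. Not stated, so assumed: two-sided alpha 0.05, 1:1 allocation, no continuity correction.

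n per arm = [1.960·√(2·p̄·q̄) + 0.842·√(p₀q₀ + p₁q₁)]² / (p₀ − p₁)², with p̄ = 0.20 and q̄ = 1 − p̄

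= [1.960·√0.320 + 0.842·√0.315]² / 0.10² ≈ 250, so N = 500. The figure reproduces, with no allowance for missing day-28 status. Expected events: 250 × 0.25 + 250 × 0.15 = 100.

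**3. Sensitivity to missed events**

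The documents give no discharge or readmission rate, so a range is assumed. Let m be the share of an arm's primary events that are non-fatal intubations after discharge and go unrecorded. Observed rate = true rate × (1 − m).

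Power = Φ{[(p₀ − p₁)·√250 − 1.960·√(2·p̄·q̄)] / √(p₀q₀ + p₁q₁)}

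The protocol reads OR > 1 as benefit of prone positioning, so the OR is taken as control over prone.

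| m control | m prone | Observed rates | OR | Power at N = 500 | N for 80% |
|---|---|---|---|---|---|
| 0 | 0 | 25.0% / 15.0% | 1.89 | 0.800 | 500 |
| 2% | 2% | 24.5% / 14.7% | 1.88 | 0.790 | 514 |
| 5% | 5% | 23.75% / 14.25% | 1.87 | 0.774 | 534 |
| 10% | 10% | 22.5% / 13.5% | 1.86 | 0.747 | 570 |

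On 100 expected events, 2% to 10% is 2 to 10 missed events in the whole trial.

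**4. If loss were confined to one arm** (illustration of direction only)

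- True 25% against 15%, loss in control only: 5% gives OR 1.77, 10% gives OR 1.65.
- Same truth, loss in the prone arm only: 5% gives OR 2.01, 10% gives OR 2.14.
- True null at 20% in both arms: 5% to 10% loss in control gives OR 0.94 to 0.88; in the prone arm, OR 1.07 to 1.14.

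Equal loss leaves the OR almost unchanged and costs some power. Unequal loss shifts the OR in either direction.

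**The case against.** The strongest defence is that the protocol does commit to day 28. Section 9.2 says the evaluation parameters are in the case report form and are collected "from the time of inclusion until the 28th day of participation". Section 6.1.2 does not say that the daily readings end at discharge. Section 12.3.2 makes the records of every department the patient passed through source documents, so a readmission to a participating hospital might be found. The case report form is not reproduced, so it may contain a readmission line.

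Part of this stands: some readmissions could be recovered, and the protocol does not rule that out. But a general commitment is not a route. Once the patient is at home, the only means named is the vital-status call. No search of records for readmissions is specified, and a readmission outside the participating hospitals would not appear in their records.

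It is also fair to say that both versions of the two-month window extend past day 28, so either can establish day-28 vital status. That mismatch needs tidying but does not by itself lose events. Similarly, interim looks are already restricted to patients followed to the endpoint, and any delay from late calls cannot be sized from the document.

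**Conclusion.** The point holds in a limited form. Between discharge and day 28, a non-fatal intubation, ICU return, NIV or high-flow use, or readmission has no stated route into the data, although the endpoints cover that time. Sections 6.1.2 and 9.2 (*will* against *may*), and the two origins of the two-month window, also need reconciling.

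The size is unknown. Under the assumed 2% to 10% equal loss, power falls to between 0.79 and 0.75; this rests on the protocol's rates, 1:1 allocation and two-sided 0.05.

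Three stronger readings are tempting but unsupported:
- *A reader might infer that these endpoints are unobserved for all discharged patients.* They are not: everything up to discharge is read daily, and a patient who is not readmitted can be classified from discharge date and vital status.
- *A reader might infer that the call is optional.* Section 9.2 alone suggests this; Section 6.1.2 and the schedule list it without condition. It is a contradiction, not a settled choice.
- *A reader might infer bias towards one arm, or a specific count of lost events.* Nothing in the document gives a readmission rate or shows that loss differs by arm. The open-label design makes unequal loss possible, not established.

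**What to change.** Amend Sections 6.1.2 and 9.2 and the schedule table so that they say the same thing:

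1. One call at day 28, with a short window, is mandatory for every patient discharged alive before day 28.
2. The call records vital status with date of death, and any readmission, ICU stay, NIV or high-flow use and intubation, each with dates.
3. Only events dated on or before day 28 count towards the primary endpoint, and days after discharge are counted as free only where the call supports it.
4. The two-month window remains as a fallback for patients not reached, with one stated origin (discharge or inclusion), also aligned in Section 8.2. Check it against the study calendar: 18 months of inclusion plus two months is at least 20 months, while the stated total is 19.

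The cost is a few questions on a call already planned, a few CRF lines and the wording changes. The maximum of 500 patients need not change. The downside is minor recall error.

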## 6.1 Summary table or diagram of the chronology of the search

|                                                                                                      | Selection
Day 1 | Inclusion/
D1 Randomization | Visits
D1 to D28
maximum | Up to two months
after inclusion |
|------------------------------------------------------------------------------------------------------|--------------------|--------------------------------|--------------------------------|-------------------------------------|
| Oral information                                                                                     | ✓                  |                                |                                |                                     |
| Collection of written consent                                                                        | ✓                  |                                |                                |                                     |
| Socio-demographic data                                                                               |                    | ✓                              |                                |                                     |
| Randomization                                                                                        |                    | ✓                              |                                |                                     |
| Positioning Explained                                                                                |                    | ✓                              |                                |                                     |
| Reminder during care for the interventional group on the positioning to adopt at least 6 hours a day |                    | ✓                              | ✓                              | ✓                                   |
| Constant Oxygen therapy levels
Become Vital status                                                |                    | ✓                              | ✓                              |                                     |
| Oxygen Therapy Flow Rate                                                                             | ✓                  |                                | ✓                              |                                     |
| Telephone call for vital status if patient discharged from hospital before 28 days                   |                    |                                |                                | ✓                                   |

## 6.2 Distinction between care and research

**TABLE: Distinction between acts related to "care" and acts added by "research"**

| Research interventions | Care-related acts, procedures and treatments | Acts, procedures added by research     |
|------------------------|----------------------------------------------|-----------------------------------------------|
| Randomization          |                                              | Randomization will be applied to all patients |
| Strategy               | Position left to the patient's discretion    | Prone position at least 6 hours / 24 hours    |

## 7 SELECTION CRITERIA

### 7.1 Inclusion criteria

- Non-intubated adult COVID-19 patients (positive PCR or imaging: typical CT scan) requiring nasal oxygen therapy at a rate of at least 3 L/min to have a peripheral saturation greater than or equal to 95%
- Patient able to manage prone positioning on their own intellectually and physically
- Lack of limitation of therapies
- Patient affiliated to a social security scheme

### 7.2 Non-inclusion criteria

- Patient aged > 80 years
- Pregnant women
- Inability to prone

### 7.3 Recruitment procedures

- Patients will be recruited in the traditional inpatient ward (pulmonology, internal medicine, infectious disease) and in critical care.
- The epidemic is currently responsible for the hospitalization of 20 to 50 patients per day in the hospitals participating in the research. Half of them will require oxygen at more than 3L/min

|                                          | Number of Subjects |
|------------------------------------------|--------------------|
| Total number of selected topics          | 500                |
| Number of centres                        | 21                 |
| Inclusion period (months)                | 18 months          |
| Number of subjects / centre              | 24                 |
| Number of topics / center / month | 4 or more          |

## 8 STOP RULES

### 8.1 Criteria and modalities for premature termination of acts/procedures/strategies practiced in the context of research

Different situations exist:

- Temporary discontinuation, the investigator should document the reason for the discontinuation and its resumption in the subject's source file and CRF

- Premature discontinuation, but subject remains in the research, until the end of their participation, the investigator should document the reason.

## **8.2 Criteria and modalities for premature termination of participation in a subject's research**

- Any subject can stop participating in the research at any time and for any reason.
- The investigator may temporarily or permanently discontinue a subject's participation in research for any reason that impacts the safety of the subject or that would be in the best interests of the subject.

In the event of premature termination of a subject's research, or withdrawal of consent, the data concerning him or her collected before the premature termination may be used.

The report card must list the various reasons for stopping participation in research:

- ☐ Adverse effect
- ☐ Other medical problem
- ☐ Personal reason of the subject
- ☐ Explicit Withdrawal of Consent.

### **Monitoring methods and collection schedule for this data:**

For the duration of the study (28 days) and up to two months after the patient's discharge from the hospital if discharged before the 28th day.

#### **8.2.1 Arrangements for replacing these persons, if applicable**

Not applicable.

#### **8.2.2 Stopping part or all of the research**

The promoter AP-HP reserves the right to permanently suspend inclusions, at any time, if it turns out that the inclusion objectives are not achieved.

## **9 EVALUATION OF EFFECTIVENESS**

### **9.1 Description of efficacy endpoints**

**Composite Outcome** : Achievement of one of the following criteria (if absent at the time of randomization):

- Use of intubation
- Death

Criteria assessed up to 28 days after inclusion

### **Secondary endpoints**

- The proportion of patients admitted to intensive care (among those who were in the conventional hospitalization department at baseline)
- Number of days alive without invasive ventilation in the first 28 days
- Number of days alive out of intensive care in the first 28 days
- Number of days alive out of hospital in the first 28 days

- Number of days alive without NIV or high-flow oxygen therapy in the first 28 days (for those who did not benefit at baseline)
- Maximum rate of oxygen therapy over the course of 28 days.

## 9.2 Methods and planned timelines for measuring, collecting, and analyzing efficacy endpoints

The evaluation parameters are provided for in the case report form and will be collected by the designated investigators from the time of inclusion until the 28th day of participation. A telephone call may be made to the patient if he or she has been discharged from hospital before the 28th day in order to collect his or her vital status.

The data noted by the patient on the "time spent in PP" data collection sheet will be collected regularly in the paper CRF by the investigators.

The data collection in the e-CRF will be done by a TEC of the F-Widal-Lariboisière CRU, following the sending of the CRF pages by the centres by photos or scans with anonymised data.

## 10 VIGILANCE

In the context of this research mentioned in 2° of Article 1121-1 of the CSP, adverse events (serious or not) are not to be notified to the sponsor. The notification must be made within the framework of the vigilance put in place in the context of care for the practice that is the subject of the research.

Nevertheless, in accordance with Article R 1123-59 of the CSP, the promoter shall inform the competent authority and the Committee for the Protection of Persons without delay of the new facts defined in 12° of Article R. 1123-46 and, where applicable, of the measures taken.

## 11 SPECIFIC RESEARCH COMMITTEES

### Steering Committee

The steering committee is made up of:

**Coordinating investigator:** [name], Department of Anaesthesia and Critical Care at Bicêtre Hospital. Organizes research on the general plan and coordinates information.

**Scientific director:** [name], Department of Anaesthesia and Critical Care at the Bicêtre Hospital. Also organizes research and coordinates information.

**Biostatistician:** [name] Lariboisière-Fernand Widal Clinical Research Unit. Determines the methodology and monitors the progress of the research with the help of the team of the Lariboisière-Fernand Widal Clinical Research Unit.

The steering committee is in regular telephone contact for the organization of the research and also meets formally by videoconference on a regular basis.

